### 9.2 Adverse events

9.2.1 Definition: "AE" is any adverse medical events occurred after the subjects have received the drug, which may be unrelated to the treatment. Accordingly, AE can be any discomforts and unaware signs (e.g. abnormal laboratory examination results), symptoms or diseases.

- ☞ All AEs must be recorded in CRF regardless of their severity and relationship with the used drug. For all the subjects who withdraw from this study due to AEs, the investigators should continue to follow-up with them until full recovery, record the relevant data, and indicate AE occurrence date and recovery date in the CRF.

9.2.2 Correlation assessment: the investigators should evaluate the correlation of the AEs with drug treatment in this trial as follows:

#### ✧ Certainly related to the trial drug

Evidence of using the trial drug; plausible time relationship between the occurrence of AE and the use of trial drug; the occurrence of AE can be more reasonably explained by the use of trial drug than other reasons; plausible response to withdrawal; positive drug rechallenge test; consistence between the AE pattern and the past understanding of this drug or this type of drugs.

#### ✧ Probably / Likely related to the trial drug

Evidence of using the trial drug; plausible time relationship between the occurrence of AE and the use of trial drug; the occurrence of AE can be more reasonably explained by the use of trial drug than other reasons; reasonable drug withdrawal response;

#### ✧ Possibly related to the trial drug

Evidence of using the trial drug; plausible time relationship between the occurrence of AE and the use of trial drug; AE may be explained by the use of trial drug or other reasons; reasonable drug withdrawal response.

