- 5) Precautions: the patients should be instructed to observe the photoreaction after drug infusion and pay attention to photo protection. The photoreaction is expected to disappear completely in approximately 10 days after drug infusion. During the light protection period (2 weeks), the subjects should pay attention to protection of the exposed skin and eyes, avoid irradiation of sunlight or strong indoor lights. In case of drug extravasation during the infusion, the extravasation area must be kept completely away from light for a fairly long time until local swelling and discoloration disappears completely, otherwise severe local skin photoinjury may occur.
- 6) PDT may cause the following treatment reactions: the patients may experience itching, burning sensation, pain, swelling, blisters and scabs at the irradiated and surrounding area. These therapeutic responses are usually transient and self-healing without special treatment.
- 7) Adverse reactions: If light protection measures are not taken properly, some patients may experience photosensitive reactions such as photosensitive dermatitis, photosensitive ophthalmia, photosensitive cheilitis, etc; some patients may experience nausea, dizziness, headache, drowsiness, total bilirubin elevation, hyperpigmentation, hypopigmentation,

treatment site infection, scarring and other adverse reactions.

- 8) At week 8 after the first treatment, if the color of treatment area has not subsided completely and there are no serious pigmentation, scarring and other conditions that are unsuitable for re-treatment according to the investigator's judgment, the next stage treatment can be carried out.

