#### ✧ Unlikely related to the trial drug

Evidence of using the trial drug; AE is more likely caused by other reasons; drug withdrawal reaction is negative or plausible; drug rechallenge test is negative or plausible.

✧ Not related to the trial drug

The subject did not use the trial drug; the time relationship between the occurrence of AE and the use of trial drug is not plausible; or some other obvious reason causes the AE.

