#### 14.5 Contents of statistical analysis

1. Case distribution: provide the sizes of different data sets of all groups, distribution of the cases among all centers, comparison of the total dropout rate, and a detailed listing of the reasons for termination.
2. Comparability analysis: demographic data and other baseline indexes are compared to measure the intergroup comparability.
3. Compliance analysis: (1) Drug compliance analysis: compare whether the patients of the two groups have taken the correct doses of trial drugs in timely manner without using the prohibited drugs and food as described in this protocol. (2) Drug combination analysis: count the number of subjects receiving drug combination in each group and provide a detailed list.
4. Efficacy analysis: PP and ITT analysis of the primary efficacy should be carried out at the same time; because this study is a multicenter clinical trial, the impact of center effect on the efficacy should be considered during analysis.
5. Analysis of the efficacy influencing factors: if there are significant differences in age, gender, disease types, disease conditions and other factors between the two groups before drug treatment or relevant factors significantly affecting the efficacy (e.g. drug combination) during the trial process, these factors should be used as covariates for analysis of covariance or logistic regression analysis during intergroup efficacy comparison.
6. Safety analysis: based on the requirements for correlation of adverse reactions, use listings to describe the AEs and adverse reactions in both groups (including the number of cases of various

AEs, the number of cases with "normal shift to abnormal" or "exacerbation of the abnormality" of the laboratory test indexes and abnormal conversion rate before and after this trial), list the causes and explain. Chi-square test is used for statistical analysis of the adverse reactions.

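### The causality grades ask for a withdrawal response that one completed infusion cannot give, so lasting harms the protocol expects have no clear grade and may be under-counted in the only named safety test

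*Protocol*

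**What the plan says.** Protocol 9.2.2 has the investigator place each adverse event in one of five grades, each defined by a string of items.

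- *Certainly related* includes "plausible response to withdrawal; positive drug rechallenge test".
- *Probably/likely related* asks that the event "can be more reasonably explained by the use of trial drug than other reasons; reasonable drug withdrawal response".
- *Possibly related* asks for "AE may be explained by the use of trial drug or other reasons; reasonable drug withdrawal response".
- *Unlikely related* requires that "AE is more likely caused by other reasons; drug withdrawal reaction is negative or plausible".
- *Not related* is met by any one of three grounds: "The subject did not use the trial drug", implausible timing, "or some other obvious reason causes the AE".

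On exposure, 4.3 item 3 has the drug infused within 20 minutes, and section 6 allows up to two treatments. Under 4.3 item 8 the second treatment goes ahead only if the investigator sees no serious pigmentation, scarring or similar bar.

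On expected harms, 4.3 item 7 lists, among adverse reactions, "total bilirubin elevation, hyperpigmentation, hypopigmentation", followed by treatment-site infection and scarring.

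On analysis, 14.5 item 6 takes the correlation requirements as its starting point, lists adverse events and adverse reactions by group, and then says "Chi-square test is used for statistical analysis of the adverse reactions". It does not say which of the five grades make an event an adverse reaction.

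**The concern.** A withdrawal item suits a drug given repeatedly: stop it and see whether the event subsides. Here the drug has already been given in full when most events appear, so nothing is left to withdraw. An event that fades has simply run its course. One that does not fade has no favourable withdrawal response to record. The item therefore says little about cause for any event, and it counts against relatedness for lasting ones.

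This matters because the grade feeds the analysis. The only safety test that 14.5 names is on adverse reactions, a count that depends on relatedness. If centers handle the inapplicable item differently, the tested count partly reflects grading habit, and the harms most exposed to this are lasting changes at the treated site. Grading is done at the site during the trial. An analysis plan can choose what to test, but it cannot recover grades assigned under a criterion that did not fit.

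**Working it through.** The protocol gives no figure on this point, and the sample size does not depend on it. The check is mainly one of logic.

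**Step 1. The grades side by side (9.2.2).**

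| Grade | Attribution items | Withdrawal item | Rechallenge item |
|---|---|---|---|
| Certainly | drug used, timing plausible, drug the better explanation, fits past knowledge | plausible | positive |
| Probably | drug used, timing plausible, drug the better explanation | reasonable | none |
| Possibly | drug used, timing plausible, drug or another cause | reasonable | none |
| Unlikely | drug used, another cause more likely | negative or plausible | negative or plausible |
| Not related | drug not used, or timing implausible, or another obvious cause | none | none |

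No row has an entry for not applicable or not assessable.

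**Step 2. A test case.** Take a scar at the irradiated site after active treatment, with plausible timing, no better explanation and no resolution by week 8. If every listed item must be met:

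- *Certainly*, *probably* and *possibly* fail on the withdrawal item.
- *Unlikely* fails because no other cause is more likely.
- *Not related* fails because the drug was used, the timing fits and no other cause is obvious.

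The event meets none of the five grades. The same holds for lasting hyper- or hypopigmentation.

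**Step 3. Rechallenge.** The only re-exposure in the trial is course 2, and 4.3 item 8 withholds it when pigmentation or scarring is serious. Those subjects can never supply a positive rechallenge. For the control group, course 2 is the first exposure to the drug, so it is no rechallenge for them either.

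**Step 4. Link to the test.** An event without a clear grade is an adverse reaction or not according to how the center resolves the gap. Section 5 plans eight centers.

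**Step 5. What partial loss could do (illustration only).** The arm sizes, 330 and 110, are from 3.1. The event rates and the share lost are assumptions; the documents give neither. With active rate p1 and control rate p0, two-sided 0.05:

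power = Φ[(p1 − p0 − 1.96·s0)/s1], where s0 = √[p̄(1 − p̄)(1/330 + 1/110)], s1 = √[p1(1 − p1)/330 + p0(1 − p0)/110] and p̄ is the pooled rate.

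For true rates of 10% v 1%:

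- All events counted: p̄ = 0.0775, s0 = 0.0294, s1 = 0.0190, (0.09 − 0.0577)/0.0190 = 1.70, power 96%.
- Half of the active-arm events not graded related (5% v 1%): p̄ = 0.04, s0 = 0.0216, s1 = 0.0153, (0.04 − 0.0423)/0.0153 = −0.15, power 44%.
- Half lost in both arms, which is closer to blinded grading (5% v 0.5%): p̄ = 0.0388, s0 = 0.0212, s1 = 0.0138, (0.045 − 0.0416)/0.0138 = 0.24, power 60%.

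Over a range of active rates, with control at 1%:

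| True active rate | All counted | Half lost, active only | Half lost, both arms |
|---|---|---|---|
| 2% | 7% | 3% | 4% |
| 5% | 44% | 10% | 17% |
| 10% | 96% | 44% | 60% |
| 20% | >99% | 96% | 98% |

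About one control event is expected (110 × 0.01 = 1.1), so the normal approximation is rough. The table shows direction only: loss matters little when the harm is frequent and much when it is moderately rare.

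**The case against.** The best defence is that 9.2.2 never says every item is mandatory. Words such as reasonable and plausible leave room for judgement, and 9.2.5 asks the investigator to decide relatedness and give evidence. An investigator who has read 4.3 item 7 would probably grade a treatment-site scar as related. That stands: it makes the problem one of inconsistency and not of certain exclusion. It does not remove the problem, because the text gives no guidance on an item that cannot be assessed.

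It can also be said that nothing is hidden: 9.2.1 records all adverse events whatever their relation, 14.5 item 6 lists them by group, and 14.2.2 allows chi-square or Fisher tests for count data in general. This stands too. The events remain visible; what is at risk is the tested count. The cut-off for an adverse reaction could be set in an analysis plan that is not shown, but the grading rule itself belongs to the protocol.

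Three stronger readings are tempting, and the documents do not support them.

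- A reader might infer that lasting harms slide into *unlikely* because that grade admits a negative withdrawal reaction. It also needs a more likely other cause, which such a scar lacks.
- A reader might infer that control events must all be *not related*, since controls received no drug in course 1. That applies only if the grader knows the allocation. Investigators are to be kept blind (4.4, section 12), unblinding follows database lock (13.4), and nothing provides for regrading afterwards.
- A reader might infer that the tested count for these harms becomes zero in both arms. That would need every center to read the rule literally and to resolve the gap the same way.

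**Conclusion.** The defect is real and should be corrected. Every related grade lists a withdrawal response that a completed infusion cannot supply, the top grade adds a rechallenge that 4.3 item 8 rules out for serious cases, and there is no way to mark either as not assessable. On a strict reading, lasting pigment change and scarring meet no grade. The supported consequence is a risk of inconsistent grading between centers and of under-counting in the one named safety test.

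The size is unknown. It depends on how often lasting harms occur and how investigators treat the item, and the documents give neither. The power figures rest on assumed rates and an assumed loss of half the events; they show that partial loss could matter, not that it will.

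**What to change.** **In 9.2.2**

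- Add a not applicable/not assessable entry for withdrawal and for rechallenge, so that neither is needed for *possibly* or *probably*.
- Have relation assessed to the trial treatment as a whole, infusion plus irradiation, with the grader blind to allocation. Section 4.3 item 6 already attributes local reactions to the photodynamic treatment as a whole.

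**In 14.5 item 6**

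- State which grades count as adverse reactions.
- Run the between-group test on all-cause adverse events of course 1, with related events as a second display. Course 1 is the only placebo-controlled period, because controls receive the drug in course 2 (3.1).
- Keep describing both stages, so that the section 2 statement on safety analysis is still met.

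**Cost:** protocol and case-report-form guidance wording, plus one more table. The downside is that more events may count as related.

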#### ✧ Unlikely related to the trial drug

Evidence of using the trial drug; AE is more likely caused by other reasons; drug withdrawal reaction is negative or plausible; drug rechallenge test is negative or plausible.

✧ Not related to the trial drug

The subject did not use the trial drug; the time relationship between the occurrence of AE and the use of trial drug is not plausible; or some other obvious reason causes the AE.

#### 9.2.3 Severity evaluation

The intensity or severity of AE falls into the following categories:

- ✧ Mild: easily tolerated AE, subjects can feel it occasionally.
- ✧ Moderate: AE is significantly discomfort and interfere with the daily activities; the subjects felt significantly but still can tolerate the symptoms without need to discontinue drug treatment.
- ✧ Severe: AE significantly interferes with normal daily activities; the subjects felt significant intolerable symptoms and discontinuation of drug treatment is required.

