## 3. Trial design

### 3.1 Design principle:

This is a parallel, placebo-controlled, double-blinded and multicenter clinical trial.

The subjects are randomized into trial group and control group at 3:1 ratio in this phase III clinical trial.

Statistical estimation of the sample size: using two-sided test of the efficacy,  $\alpha=0.05$  and  $\beta=0.1$  (power=90%) based on phase II clinical trial results, the expert panel estimates the total clinical efficacy rate of hemoporphin for injection to be 75.0% in the treatment of port-wine stains and expects a 40% difference from the placebo group; consequently, the estimated minimal number of subjects is 66 for the trial group and 22 for the control group.

In compliance with the SFDA requirement of minimum sample size of no less than 300 subjects for phase III clinical trial group, and also taking into account of dropout, the sample size of this clinical trial was determined to be 330 subjects for the trial group and 110 subjects for the control group, giving a total of 440 subjects.

The subjects will be assigned into trial group or control group by stratified block randomization to receive not more than 2 courses of treatment. The control group receive placebo during the first course of treatment followed by trial drug during the second course of treatment. Each course of treatment will last for 8 weeks. Based on the phase II clinical trial results, the trial drug dose is set at 5mg/kg.

The trial design profile is shown in the following table.

| Trial period                   | Hemoporphin for injection dose | Group and number of cases     | Design principle                                                          |
|--------------------------------|--------------------------------|-------------------------------|---------------------------------------------------------------------------|
| The first course of treatment  | 5mg/kg                         | 330 subjects in trial group   | Randomized, double-blinded, placebo and parallel-controlled (multicenter) |
|                                | 0mg/kg                         | 110 subjects in control group |                                                                           |
| The Second course of treatment | 5mg/kg                         | 330 subjects in trial group   | Randomized, double-blinded (multicenter)                                  |

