#### 4.3 Treatment methods

- 1) Hemoporphin solution is prepared per the trial dose. The prepared drug solution is a dark red transparent liquid and should be inspected for precipitation or discoloration phenomenon prior to injection.
- 2) The injection site skin is sterilized routinely.
- 3) Intravenous infusion of the drug solution should be at a constant speed using an infusion pump, and be completed within 20min. The relatively large veins easily protected from exposure to light should be selected (the largest vein in the arm such as the median cubital vein is preferred and small veins in the back of the hand should be avoided); 1ml physiological saline is injected for confirmation prior to drug infusion to prevent drug leakage into the extravascular space. Additional 2~4ml physiological saline should be infused at ending of drug infusion to decrease the intravascular drug concentration in order to prevent

photosensitive reactions at the injection site. The photosensitizers should be protected from light during the preparation and injection process to avoid efficacy decline. Measures should be taken to protect the subjects from light after drug infusion.

- 4) The target lesions are irradiated with 532nm laser and irradiation power density of 80-100 mW/cm^2.

☞ Irradiation time: the laser irradiation begins 10min after beginning of drug infusion and ends 20min later. The total irradiation time is 20 minutes.

☞ Precautions during laser irradiation: ① depending on the lesion size and site, the selected treatment areas should be as flat as possible; the hair-covered areas (eyebrow, beard and hairline) need to be shaved clean to avoid affecting laser irradiation. The non-treatment area surrounding the lesion, especially the nasolabial fold and other weak areas should be carefully covered with adhesive tapes and double-layer red-black clothing; ② the output power at the fiber terminal should be adjusted and measured according to the therapeutic regimen prior to irradiation, the beam expander should be maintained perpendicular to the irradiation surface; in addition, it is necessary to pay attention to the size of the beam spot, closely observe the changes in the irradiated areas, and accurately control the irradiation time; ③ the output power need to be monitored before, after and during the irradiation process.

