### 9.3.4 The observer should provide the following information in SAE reports:

- ✧ Observer's name and center code
- ✧ Initials of the Subject's name
- ✧ Subject's general data including age, date of birth, marital status and body weight
- ✧ SAE details including descriptions of the affected body site, severity and the criteria for determining severity
- ✧ Description
- ✧ Occur date

- ✧ End date or duration of the AE
- ✧ Severity
- ✧ Treatment (including hospitalization)
- ✧ Causal relationship with the trial drug
- ✧ Outcome: recover or having sequelae
- ✧ Adjustment of drug treatment
- ✧ Measures taken for trial drug such as stopping treatment or continuing treatment, etc
- ✧ For life-threatening events, the cause of death and the possible relationship should be provided
- ✧ Autopsy findings
- ✧ Drug number
- ✧ Indication of the used drug or the trial drug
- ✧ Formula or concentration of the drug
- ✧ Daily dose and regimen
- ✧ Route of administration
- ✧ Other treatments: the investigators should provide information on the relevant products for concomitant drugs (including over-the-counter drugs) and non-drug therapies
- ✧ Other information: any information that can help understanding the events such as allergy, drug or alcohol dependence, family history, special examination findings.

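### Section 9.2.3 ties the severe grade to stopping the drug, so an intolerable event that needs no discontinuation has no valid grade, and after a subject's last infusion no event can meet severe as written

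*Protocol*

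**What the plan says.** Section 9.2.3 of the protocol defines three grades.

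- Mild is an easily tolerated event.
- Moderate interferes with daily activities, but "the subjects felt significantly but still can tolerate the symptoms without need to discontinue drug treatment".
- Severe interferes significantly with daily activities, and "the subjects felt significant intolerable symptoms and discontinuation of drug treatment is required".

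Section 4.3 describes the dosing: "Intravenous infusion of the drug solution should be at a constant speed using an infusion pump, and be completed within 20min". For the light, "the laser irradiation begins 10min after beginning of drug infusion and ends 20min later". Section 3.1 has subjects assigned "to receive not more than 2 courses of treatment" and adds: "Each course of treatment will last for 8 weeks". Section 4.3 (item 8) and section 6 give the second course only if the treated area has not cleared. Item 8 also lets the investigator withhold it because of pigmentation, scarring or other conditions. Section 10.2.1 separately allows withdrawal because of an adverse event.

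For serious adverse event reports, section 9.3.4 lists severity as one item and, as another, "Measures taken for trial drug such as stopping treatment or continuing treatment, etc".

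**The concern.** A severity grade should describe how intense an event is. Here the top grade also demands an action on the drug, joined by *and*, while the middle grade excludes that action. That wording suits a drug taken daily. It suits a drug given in one short infusion badly, because the expected reactions (section 4.3, items 5 to 7: pain, swelling, blisters, scabs, photosensitive reactions, scarring) can arise or persist after dosing has ended.

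What is at stake is the severity description of the safety profile. Section 2 has the safety analysis cover both courses, and section 12 asks for uniform determination criteria at all sites. If the definitions leave an intolerable event without a grade, each investigator has to improvise one.

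**Working it through.** The protocol gives no figure to reproduce on this point. The check is mainly one of logic, with one small calculation.

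**Step 1: do the grades cover all cases?** Leave aside mild events and cross two attributes, whether symptoms are tolerable and whether discontinuation is required.

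- Tolerable, discontinuation not required: moderate.
- Intolerable, discontinuation required: severe.
- Intolerable, discontinuation not required: not moderate, because it is not tolerable; not severe, because the drug need not be stopped. No grade.
- Tolerable, discontinuation required: also outside both definitions, although the point here rests on the third case.

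**Step 2: when can discontinuation be required?**

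- *During an infusion.* It can be stopped. This window is at most 20 minutes per course. If *drug treatment* is read to include the light, irradiation runs from minute 10 to minute 30 (10 + 20), so the window closes at minute 30.
- *After course 1, with course 2 still due.* The condition can be met by withholding course 2 (section 4.3, item 8, judged at week 8) or by withdrawing the subject (section 10.2.1, not tied to week 8).
- *After course 1, with no re-treatment due because the lesion has cleared.* No drug remains.
- *After course 2.* No drug remains.

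Section 4.3 expects the photoreaction to be gone about 10 days after infusion and describes treatment reactions as mostly short-lived. An intolerable reaction on Day 3 of course 1 that has healed by week 8 need not prevent course 2. Unless the subject is withdrawn, that event falls in the ungraded case even though course 2 lay ahead.

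**Step 3: how many courses have no later course to withhold?** Assume that all 440 planned subjects receive course 1 and that a share f receives course 2. The documents do not give f. Courses given are 440 + 440f, and each subject has exactly one last course, so the share of last courses is 440/(440 + 440f) = 1/(1 + f).

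- f = 1: 440/880 = 50%
- f = 0.75: 440/770 = 57%
- f = 0.5: 440/660 = 67%

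For f below 1 these are upper values for the affected courses. Some subjects without a second course may have had it withheld because of an adverse event, and for them the condition was met. These are shares of courses, not of events.

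**Step 4: what depends on the grade?** Section 9.2.1 requires every adverse event to be recorded whatever its severity. Section 9.3.1 defines serious events by outcome, not by this scale. Section 14.5 (item 6) plans listings, laboratory shifts and a chi-square test of adverse reactions; it names no analysis by severity grade. The effect is therefore confined to the grade itself and to any description of severity built on it.

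**The case against.** The strongest reply is that treatment is not a single infusion. A second course is planned 8 weeks later, and not giving it is an ordinary meaning of discontinuing treatment. This stands, and it limits the point. A reader might infer that only events starting in the 20 minutes of infusion can be severe, against 56 days (8 × 7) of follow-up. The documents do not support that for course 1, where withholding course 2 or withdrawing the subject remains possible.

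A reader might also infer that severe events will be under-counted. That is a plausible direction, but not one the documents show. Faced with intolerable symptoms that clearly disrupt daily life, an investigator may well choose severe, since the intensity elements are met and moderate is excluded by its own wording.

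Nor do the documents support a bias concentrated in the active arm. The placebo comparison exists only in course 1, where the condition can still be met by subjects due a second course. In course 2 both groups receive the drug.

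Finally, no event is lost and no planned test changes (step 4). That also stands, and it keeps this a grading matter. It does not close the gap in the definitions: an investigator who follows them exactly has no grade to enter, and one who improvises may do so differently from a colleague at another centre.

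**Conclusion.** The point holds in this form. As written, section 9.2.3 leaves an intolerable event without required discontinuation ungraded. It makes severe unattainable for any event arising after a subject's last infusion, and after course 1 attainable only by withholding course 2 or withdrawing the subject. Severe events may be under-graded or graded inconsistently across centres.

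The size cannot be derived. If every subject is re-treated, half of all courses have no later course to withhold; for lower re-treatment shares, 57% and 67% at f = 0.75 and 0.5 are upper values under an assumed f. How many events would fall in the gap, and whether the arms would differ, is not in the documents. The conclusion rests on reading the *and* in the severe definition literally and on taking *drug treatment* to mean the trial infusions. The correction should be made, but the point bears on neither the efficacy conclusion nor the detection of adverse events.

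**What to change.** In section 9.2.3, define mild, moderate and severe by tolerability and interference with daily activities alone, and delete the references to discontinuing drug treatment in the moderate and severe definitions. Add a separate CRF item for action taken with the trial drug, completed for every adverse event, in line with what section 9.3.4 already asks for serious ones. This alters no dose, withdrawal rule or re-treatment criterion.

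The cost is two phrases in the protocol, one CRF item and a matching line in the completion guide. The downside is that a few more events may be graded severe.
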